### Qualitative data analysis

Interviews will be recorded and transcribed verbatim and manually coded line-by-line. Transcripts will be subjected to Framework Analysis, [33] allowing comparisons within and between transcripts. QSR N-Vivo 11 will be used to manage the dataset. A multi-disciplinary team will be involved in analysis to ensure reflexivity. The resulting data will be cross-referenced with quantitative data to provide greater richness to the data-set. This data will also be critically interrogated as part of the ethical analysis. [34]

### Ethical analysis

Ethical concepts and analysis will be relevant throughout this project, and will be iteratively and critically reflected upon as the study progresses. Quantitative survey items allowing free-text responses regarding benefits and drawbacks of TGP will allow the study team to see whether any responses assist in identifying relevant ethical themes; such as how participants view autonomous decision-making or cost considerations. Data from qualitative interviews will be critically compared with bioethics literature regarding concepts such as family communication, duties to disclose, what constitutes autonomous decision-making, approaching uncertainty in TGP, the distinction between research and clinical practice, obligations at the conclusion of a research project and determining when it is appropriate to offer testing; and to whom. The result will be a series of normative positions, defensible using ethical reasoning and informed by empirical data.

### Quantitative data analysis

Mean differences in outcomes will be compared using t-test (continuous) or chi-squared tests (dichotomous). Non-parametric tests will also be used where appropriate. Temporal changes in scales will be investigated by calculating the difference between time-points. Multiple (continuous outcomes) or logistic (dichotomous outcomes) regression will be used to adjust for the effect of confounders and identify predictors of outcome. Linear mixed models and logistic mixed models will be carried out in R: A language and environment for statistical computing using package nlme for the linear mixed model and lme4 for the logistic mixed model. Assumptions of normality of residuals and homogeneity of variance will be checked visually though diagnostic residual plots. Multivariable models will be constructed with the inclusion of all potential confounders, and those predictors that show weak evidence for an association with the outcome in univariate analysis. Backwards elimination followed by forwards addition will be used to select predicting variables in the final model. Known and identified confounders will be included regardless of their statistical significance. Collinear independent variables will be identified and removed.

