## Methods/design

### Aims and hypotheses

The aim of this study in adults with advanced cancer undergoing TGP is to:*Before and after receipt of results:* evaluate knowledge of TGP, preferences for genetic information, attitudes (positive and negative) and the value placed on TGP;*After receipt of results:* identify behavioural, decisional and psychological outcomes from TGP along with their respective predictors; andContextualize the findings via a critical bioethics analysis.

Specific hypotheses are that:At baseline (after giving informed consent to undergo TGP), advanced cancer patients will have moderate to poor knowledge about TGP (< 55% correct on knowledge scale).At baseline, advanced cancer patients will have primarily positive attitudes to, and highly value, TGP.Of advanced cancer patients *who receive an actionable result*, most will:Pursue personalised treatment in a clinical trial setting (behavioural outcomes).Cope well with results, and experience low decisional conflict and regret and high decisional satisfaction (decisional outcomes).Have higher hope, less cancer-related anxiety, lower fear of cancer progression and lower general anxiety and depression than those who do not receive actionable results (psychosocial outcomes).Those advanced cancer patients who have *no actionable variants identified* will:Struggle to cope with non-results (decisional outcomes).Have levels of hope, cancer-related anxiety, fear of cancer progression and general anxiety and depression similar to published results for advanced cancer patients who have not undergone TGP, within 1 month of receiving results and 5 months later (psychosocial outcomes).5.Predictors of behavioural, decisional and psychological outcomes within 1 month of receiving results and 5 months later, will include:Age, education level, ethnicity, and gender;Tolerance of uncertainty and baseline knowledge; andPreferences and attitudes to TGP.

Methodology in critical bioethics analysis is not hypothesis-driven and to this end there are no hypotheses relating to this part of the analysis.

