### Coping with uncertainty

Eight Likert-scale items from Kasparian et al., [21] measuring reaction to uncertainty, ambiguity and the future. High scores indicate greater intolerance.

Note that to reduce participant burden at baseline, measures of psychological morbidity (anxiety, depression, hope) were not included at T0.

The following outcome measures will be administered at the first follow-up only:

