### Satisfaction with decision to have TGP

The 6-item Satisfaction with Decision scale [29] measures satisfaction with decision to have TGP. Items are rated on a Likert scale. High scores indicate greater satisfaction.

The following outcome measures will be administered at baseline and all follow-ups:

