### Fear of cancer progression

Three items from the Concerns about Recurrence Questionnaire [30], adapted to measure fear of cancer progression. High scores indicate greater fear.

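### The plan does not fix the T0 fear-of-progression score as a covariate, or name the deciding analysis, for hypothesis 3's contrast between non-randomised result groups

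*Protocol article*

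**What the plan says.** All places are in the protocol article.

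- **Hypothesis (Aims and hypotheses).** Patients with an actionable result are expected to have, among other things, "lower fear of cancer progression and lower general anxiety and depression than those who do not receive actionable results". The groups are formed by the test result.
- **Measure.** The Fear of cancer progression section describes "Three items from the Concerns about Recurrence Questionnaire [30], adapted to measure fear of cancer progression". Its lead-in reads "The following outcome measures will be administered at baseline and all follow-ups", and Table 1 agrees: T0, T1 and T2.
- **The other psychological outcomes of hypothesis 3.** To limit burden at baseline, "measures of psychological morbidity (anxiety, depression, hope) were not included at T0". Table 1 also shows no T0 assessment for the Impact of Events Scale. Fear of progression is therefore the only one of these outcomes with its own pre-result value.
- **Analysis (Quantitative data analysis).** "Mean differences in outcomes will be compared using t-test (continuous) or chi-squared tests (dichotomous"; "Temporal changes in scales will be investigated by calculating the difference between time-points"; and multiple or logistic "regression will be used to adjust for the effect of confounders and identify predictors of outcome". Linear and logistic mixed models are also planned. Known and identified confounders stay in the model whatever their significance, other predictors pass through univariate screening and stepwise selection, and collinear variables are removed. No confounder is named, and the T0 value of an outcome is not mentioned.

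**The concern.** A t-test on follow-up scores tests whether the group means are equal after results are returned. In non-randomised groups that is a different question from whether the result changed anything. The Knowledge section of the article lists, as a quiz topic, the cancers in which informative results are more likely, so result status is linked to cancer type. Cancer type and prognosis could plausibly relate to fear before testing, although the article gives no data on this.

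The T0 score is the direct safeguard, and it is already collected. If it is left out of the deciding analysis, a prior difference can pass for a consequence of the result, or hide one. Precision is also lost in a contrast already limited by a small actionable group.

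**Working it through.** **Inputs from the Sample size section:** at fewest 469 patients, 15% actionable, significance level 0.05, 90% power, SD 15 on the Impact of Events Scale. This gives 0.15 × 469 ≈ 70 actionable and 399 not.

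**Assumptions:** a two-sided test; a T0-to-follow-up correlation r for fear of progression, which the article does not give (range 0.3 to 0.8); equal SDs at T0 and follow-up.

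**The plan's own group-contrast figure.** The only powered group contrast is 4.5 points on the Impact of Events Scale. The detectable difference is SD × (1.960 + 1.282) × √(1/n₁ + 1/n₂).
- 70 v 399: 15 × 3.242 × 0.1296 = 6.30 points. Power at 4.5 points is 64%.
- Equal halves of 234.5: 4.49 points.

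The 4.5 therefore does not reproduce from a 15% split with SD 15; it does with equal groups. That is a separate matter. It bears on this point because no power is stated for fear of progression, and because 4.5/15 = 0.30 SD serves below only as a benchmark effect.

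**Precision for fear of progression, 70 v 399, in SD units.** Residual variance is 1 for a follow-up-only t-test, 2(1 − r) for a change score and 1 − r² for a T0-adjusted model. The detectable difference at 90% power is 3.242 × 0.1296 × √variance = 0.420 × √variance.

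| r | t-test | change score | T0-adjusted | power at 0.30 SD (same order) |
|---|---|---|---|---|
| 0.3 | 0.420 | 0.497 | 0.401 | 64% / 50% / 68% |
| 0.5 | 0.420 | 0.420 | 0.364 | 64% / 64% / 76% |
| 0.6 | 0.420 | 0.376 | 0.336 | 64% / 74% / 83% |
| 0.7 | 0.420 | 0.325 | 0.300 | 64% / 85% / 90% |
| 0.8 | 0.420 | 0.266 | 0.252 | 64% / 96% / 97% |

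The Discussion expects only 5–10% actionable. At 469 patients that is about 23 v 446 or 47 v 422, and the unadjusted detectable difference becomes 10.397/15 = 0.69 SD or 7.477/15 = 0.50 SD.

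**Bias, illustration only.** Assume a T0 gap of 0.2 SD, r = 0.6 and no effect of the result. The standard error is 0.1296 for the t-test, 0.1296 × √0.8 = 0.116 for the change score and 0.1296 × 0.8 = 0.104 for the adjusted model. The rejection rate at nominal 5% follows from bias divided by standard error.

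| If, without any effect, the gap would | t-test | change score | T0-adjusted |
|---|---|---|---|
| shrink by the factor r | bias 0.12, about 15% | bias −0.08, about 11% | bias 0, 5% |
| persist in full | bias 0.20, about 34% | bias 0, 5% | bias 0.08, about 12% |

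In both cases T0 adjustment is closer to nominal than the t-test. Between T0 adjustment and the change score, the order reverses with the assumption.

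**The case against.** The strongest reply is that the t-test is only the first sentence of the analysis section. The section also plans confounder-adjusted regression and mixed models, and keeps known and identified confounders regardless of significance. If T0 fear differs by result group and predicts later fear, it is a potential confounder under that rule. This is also a condensed article, and a full covariate list commonly sits in the analysis plan. **This stands in part.** A reader might infer that the contrast will be tested only by a t-test or a difference score; the text does not support that. But it does not secure the adjustment either. The Sample size section sizes the group contrast as a plain mean difference and sizes regression separately, for explanatory variables. The predictors in hypothesis 5 do not include the T0 outcome score. A mixed model that treats T0 as an ordinary response gives, in complete data, the change-score contrast.

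A reader might also infer that the difference score counts the T0 gap as an effect of the result. It does not: it subtracts the gap. It is unbiased if the gap would persist, and biased in the opposite direction to the t-test if the gap would shrink. This is Lord's paradox, and the documents cannot settle it. The article also ties differences to change over time, not expressly to the group contrast.

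Two extensions are tempting and not supported. Hypothesis 3 does not compare decisional satisfaction between result groups; it says most patients with an actionable result will be satisfied. Forcing T0 fear into the models for the Impact of Events Scale, the Hospital Anxiety and Depression Scale and hope would be a preference, since those scales have no T0 value of their own.

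**Conclusion.** The point holds for fear of progression only. The article names a t-test for comparing means and gives a detailed rule for selecting covariates, yet neither fixes the T0 score in the hypothesis 3 contrast nor identifies the deciding analysis.

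The precision cost of a follow-up-only test is firm in direction for every correlation considered and modest to substantial in size. Against the t-test, the detectable difference falls by about 5% at r = 0.3 (0.420 to 0.401 SD), 20% at r = 0.6 (to 0.336) and 29% at r = 0.7 (to 0.300). The correlation is an assumption, and the 0.30 SD benchmark is borrowed from a different scale.

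The false-positive rates are illustrative only, because both the T0 gap and the correlation are assumed. They show that ignoring T0 is the weakest choice under either scenario. They do not show that covariate adjustment is always unbiased.

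**What to change.** In Quantitative data analysis, state that the actionable v non-actionable contrast in fear of progression at T1 and T2 is estimated from the planned regression or mixed model, with the participant's T0 score always retained alongside the other confounders and exempt from stepwise and collinearity removal. State that this analysis decides hypothesis 3 for fear of progression and that the t-test is descriptive. If the mixed model is used, say how T0 enters it. Report the change-score contrast as a sensitivity analysis, and explain that agreement between the two makes the conclusion robust to whether a T0 gap would have persisted.

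The cost is one or two sentences, one degree of freedom per model and no new data. Patients without a T0 score need a stated handling, such as a mixed-model form that keeps them or imputation.

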### Sample size

The MoST study plans to recruit 1000 patients over three years. Thus, with a conservative retention and survival estimate of 75%, this is reduced to at fewest 469 patients. With this sample size estimate, assuming 15% of patients receive an actionable result and using a significance level of 0.05, this project: has 90% power to detect a mean change of 5.8 and 2.6 points on the Impact of Events scale for patients with actionable and non-actionable results respectively (paired t-test, SD = 15) [32] and a mean difference of 4.5 points between patients with actionable and non-actionable results; Multiple regression with at most 24 explanatory variables (including dummy variables) has 90% power to detect significant categorical variables with 5 categories (largest possible categorical variable) when that predictor explains greater than 3.6% of the residual variance, or to detect a continuous variable when it explains more than 2.3% of the residual variance. For patients with actionable results only (at fewest 70), at 80% power the minimum variance explained for continuous variables would be 12% of the residual variance, and 15% for binary predictors. For logistic regression when outcomes are on average equally likely the power to detect an odds ratio of 1.4 is 95% or 80% when the other covariates explain zero, or 37% of the outcome variance respectively. For only those with actionable results, there is 80% power to detect an odds ratio of 2.14 or greater if the other outcomes explain zero outcome variance.

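### Hypothesis 5 names its predictors in advance, but univariate screening and stepwise selection can remove their adjusted estimates and bias those that survive, mainly for weak effects and in the small actionable-result group

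*Protocol article*

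**What the plan says.** Under Aims and hypotheses, Hypothesis 5 states that predictors of the behavioural, decisional and psychological outcomes "will include:Age, education level, ethnicity, and gender;Tolerance of uncertainty and baseline knowledge; andPreferences and attitudes to TGP". That is eight constructs fixed before any data are seen.

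Under Quantitative data analysis, the multivariable models take in all potential confounders and, beyond those, only "those predictors that show weak evidence for an association with the outcome in univariate analysis". The next step is: "Backwards elimination followed by forwards addition will be used to select predicting variables in the final model". One exemption is given: "Known and identified confounders will be included regardless of their statistical significance". The article does not say which variables count as confounders, gives no p-value threshold for either step, and does not exempt the Hypothesis 5 predictors.

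Under Sample size, the power statement refers to "Multiple regression with at most 24 explanatory variables" and gives detectable effects for one predictor: 2.3% of residual variance for a continuous variable at 90% power in the full sample ("this is reduced to at fewest 469 patients"), and 12% at 80% power in the actionable-result group of at least 70.

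**The concern.** A hypothesis that names its predictors is answered by an adjusted estimate and interval for each of them. Here the data decide which predictors get one. A named predictor that misses the univariate screen, or is eliminated later, has no adjusted coefficient. A reader then cannot tell a precise null from an imprecise estimate that happened to miss the threshold.

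The survivors are kept because their estimates were large relative to their standard errors, so on average they overstate the true effect. Ordinary confidence intervals from the final model do not allow for that. The problem grows as power falls, so the actionable-result group is the most exposed. The selection rule is stated outright as the analysis; it is not a detail left open for the analysis plan.

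**Working it through.** **1. The plan's own figures.** Inputs from Sample size: N=469; actionable share 15%, giving 0.15 × 469 = 70; k = at most 24 variables; significance level 0.05. For one continuous predictor in a model that is not chosen from the data, the test is F with 1 and N − k − 1 degrees of freedom and noncentrality f² × N, where f² is the share of residual variance explained.

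- N=469, k=24, df 1 and 444, 90% power: f² = 2.25% (stated 2.3%).
- n=70, k=24, df 1 and 45, 80% power: f² = 11.7% (stated 12%).

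Both are reproduced. They hardly depend on k: with k=8 the same formula gives 2.25% and 11.6%.

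**2. Which predictors are exposed.** Of the eight constructs, age, education, ethnicity and gender may be held in the model as confounders; the article does not say. Nothing in the article protects the other four: tolerance of uncertainty, baseline knowledge, preferences and attitudes.

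**3. Effect of selection.** Simulation of linear regression with 4 true predictors of equal strength among 24 candidates, pairwise correlation 0.2, univariate screen at p<0.20, then backward and forward steps at p<0.05; 800 runs per row. The thresholds, the correlation and the number of true predictors are assumptions. Ratio is mean estimate divided by true value; coverage is that of the nominal 95% interval. The stepwise ratio and coverage are for true predictors that were kept; the fixed model contains all 24 variables.

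| n | True effect (% of residual variance) | Kept | Ratio, stepwise | Coverage, stepwise | Ratio, fixed | Coverage, fixed |
|---|---|---|---|---|---|---|
| 469 | 0.5 | 39% | 1.74 | 0.875 | 0.98 | 0.948 |
| 469 | 1 | 62% | 1.34 | 0.922 | 1.00 | 0.950 |
| 469 | 2.3 (design limit) | 92% | 1.06 | 0.964 | 1.00 | 0.948 |
| 70 | 2.3 | 30% | 2.02 | 0.802 | 0.99 | 0.956 |
| 70 | 5 | 50% | 1.49 | 0.894 | 1.00 | 0.953 |
| 70 | 12 (design limit) | 82% | 1.13 | 0.931 | 1.00 | 0.946 |

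**4. Sensitivity.**
- Only 8 candidates, n=70: ratio 2.09, 1.51 and 1.12 at 2.3%, 5% and 12%; coverage 0.79, 0.895 and 0.95. The bias does not come from having 24 candidates.
- Looser retention, n=70: at p<0.10 with a 2.3% effect, ratio 1.85 and coverage 0.855; with screening at p<0.25 and retention at p<0.157 and a 5% effect, ratio 1.33 and coverage 0.90.
- 24 independent covariates with a true coefficient of 0.2 SD (0.2² = 4% of residual variance), n=70: ratio about 1.6, with coverage between 0.88 and 0.93 over separate sets of runs.
- Repeat simulations gave coverage of 0.78 to 0.80 in the weakest n=70 setting.

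**5. What a fixed model does not change.** With one true predictor among 24, 23 are noise, and 23 × 0.05 = 1.15 are expected to reach p<0.05 in a fixed model. Simulated counts were 1.15 (fixed) against 1.22 (stepwise) at n=469, and 1.19 against 1.47 at n=70.

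Nor does it raise power. At n=70 with a coefficient of 0.2 SD, stepwise dropped the predictor in 64% of runs, while the fixed model failed to reach p<0.05 in 75%. If readers keep only the significant coefficients of the fixed model, the inflation returns: 1.91 against 1.58 for stepwise at n=70, and 1.32 against 1.30 at n=469 with a coefficient of 0.1 SD.

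**The case against.** Several stronger readings are tempting, and the article does not support them.

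- **A named predictor disappears altogether.** It does not: the univariate step gives every candidate an unadjusted estimate. Only the adjusted one can be lost.
- **Selected estimates will be presented as if the model had been fixed.** The article is silent on how they will be reported. It states no correction for selection, and no more than that can be said.
- **All eight constructs are at risk.** Up to four demographic ones may be protected as confounders.
- **The power paragraph contradicts the analysis.** Its 24 variables are an upper bound, a smaller selected model fits within it, and the stated limits barely move with the number of variables. What can be said is that the calculation describes a test in a model not chosen from the data.
- **Stepwise selection is what lets noise variables in.** The counts are nearly the same in a fixed model.
- **Intervals are generally too narrow.** At the design-limit effects, coverage is near nominal.

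It can also be argued that the stated aim is to identify predictors in an observational survey, and that the abstract's primary outcomes are knowledge, preferences, attitudes and values rather than the Hypothesis 5 outcomes. That limits the seriousness. It does not remove the point: Hypothesis 5 stands among the specific hypotheses with its predictors named, and the article nowhere calls this modelling exploratory.

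**Conclusion.** The concern holds in a limited form. A rule stated in the plan can remove the adjusted estimate of a predictor named in advance, and it keeps the survivors on their significance. This merits a change to the analysis text; it does not invalidate the study.

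At the effects the study is designed to detect, the bias is about 6% at N=469 and 12 to 13% at n=70, with coverage of 0.93 or more. Below them it is about 1.3-fold at N=469 for a 1% effect, and about 1.5- to 2-fold at n=70 for effects of 5% down to 2.3%, with coverage of roughly 0.78 to 0.93. These sizes rest on the assumed thresholds, effect sizes, correlation and number of candidates, and on linear models only. The upward bias appeared in every setting shown, but it is minor at the design limits.

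The actionable group may be smaller than 70. The Discussion expects 5 to 10% actionable, which is 23 to 47 of 469. With 23 patients a 24-variable model cannot be fitted at all (23 − 25 = −2 residual degrees of freedom).

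**What to change.** For each outcome, pre-specify one model containing all Hypothesis 5 predictors and a listed set of known confounders, with no univariate screen and no stepwise step. Report every adjusted coefficient with its confidence interval regardless of significance; without that reporting rule the gain in bias and coverage is lost. Keep the stepwise model, if wanted, as an analysis labelled exploratory.

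In the actionable-only group, use a short list of predictors named in advance, or estimate result-type interactions in the full sample.

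This changes analysis text only and needs no new data. The price is a less parsimonious model with slightly wider intervals. It should be justified by unbiased and complete estimates for the named predictors, not by fewer false positives or more power.
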